## PROTOCOL SYNOPSIS

Compound: Methyl-aminolevulinate (MAL, Metvix®)

Study code: NTNU 2011-01

EudraCT: 2011-004797-28 NO 20120327

Study title: A randomized, controlled-blinded, multi-centre study of photodynamic therapy with methyl-aminolevulinate comparing a simplified regime with the approved regime in patients with clinical low-risk superficial and nodular basal cell carcinoma

Study centres: The study will intend to include 9 centres in Norway.

Study period:

|                            |         |
|----------------------------|---------|
| Start of recruitment       | Q1 2012 |
| End of recruitment         | Q3 2012 |
| Last treatment             | Q4 2012 |
| End of 12-months follow-up | Q4 2013 |
| End of 36-months follow-up | Q4 2015 |

**Objectives** The primary objective is to compare BCC lesion response rate to a schedule using one single treatment of Metvix® PDT session with re-treatment of non-complete responders by 3 months with the response of two standard Metvix® PDT treatment sessions one week apart.

Secondary objectives are to investigate the treatment response in relation to clinical and histological tumour characteristics as tumour thickness, subtype and immunohistochemical markers.

**Study design** Randomized, controlled blinded multi-centre study.

**Procedure** Lesion mapping will take place before treatment and at the preset follow-up visits by recording the number and location of the lesions in the CRF. Registration of the lesion clinical extent, location, thickness and subtype will be done at baseline and marked on a form and/ or photographed for later identification. In order to facilitate access of the Metvix® cream and light to all parts of the lesion, the surface of BCC lesions with 5 mm of the surrounding tissue of normal appearance should be prepared using a small dermal curette. The curettage should be performed by scraping in a checked pattern for optimal removal of scales and crusts, and to roughen the surface of the lesion. Thicker lesions require debulking. Metvix® cream will then be applied in a 1.0 mm thick layer to the whole treatment field and then covered using a dressing to avoid any ambient light exposure. Metvix® is applied for 3 hours before the dressing and remnants of cream are removed. Anaesthesia using subcutaneous infiltration anaesthesia without adrenaline will be given individually at the discretion of the investigator. The treatment area is then illuminated using Aktelite CL 128

(Photocure ASA) as a light source; peak wavelength around 631 nm (redlight) and light dose 37 J/cm^2 and exposure time 7-9 minutes. After light treatment each lesion will be randomized to one or two possible treatment regimes; a single MAL-PDT treatment session with re-treatment if there is a non-complete response after 3 months (regimen 1), or two treatment sessions separated by one week (regimen 2).

Two independent pathologists will examine the HES stained diagnostic punch biopsies. Tumour thickness and subtype will be recorded. Various immunohistochemical stains will be used to evaluate their utility for enhanced detection of residual tumours.

**Endpoints** The primary endpoint will be lesions response rate and cosmetic outcome determined by clinical assessment (visual inspection and palpation) 1 and 3 years after Metvix® PDT treatment. Clinically suspected recurrences will be examined by histology. We will report the number of lesion in need of a re-treatment 3 months following the first treatment session in regime 1. Further, report on number and time of lesion to relapse by either regime, 1 or 3 years after PDT and report on adverse events in a period of up to 3 months following last treatment session.

The secondary endpoint will be to investigate relationship between clinical and pathological tumour characteristics and tumour recurrences and histopathological tumour features as BCC tumour thickness and subtypes. Tumour thickness and subtype will be established by investigation of the prepared slides from the diagnostic punch biopsies. Using immunohistochemical techniques various antibody-targeted properties will be studied in recurrences and tumours with complete response. Several tumour related markers to examine the expression pattern of markers accordingly to the invasiveness and histopathological differentiation of BCC will be studied.

**Patients** Females and males above 18 years with primary, histological confirmed BCC lesions located outside mid-face-H-area.

**Sample size** Patients with at least 374 lesions (187 in each group) will be included in the study.

## Statistics

Simple tabulation as well as logistic regression with lesion recurrence (yes/no, a binary variable) at 3 years will be employed to analyze the outcome. As one patient may yield more than one lesion, a mixed effects model with patient identity as random factor will be considered. Different lesions within the same patient will be subject to stratified randomization. The expected cure rate at 3 years (reference) is set to 80 %. The study aims to detect an experimental success rate of no less than 70 % (the non-inferiority margin 10 %). With a sample size of 170 lesions per group, a difference between the two treatment regime groups of at least 10% can be found with a significance level of 5% and a power of 80%.

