### **8.2.1 Disposition of Lesions**

The number of lesions which are included into the study, which receive Metvix® cream, which are included in safety and/or efficacy evaluation, and which complete each phase of the study, as well as withdrawals will be summarized using counts and percentages of lesions.

Each lesion will be identified, randomized, treated and followed up individually. Patient identification will be recorded anonymously, to account for potential individual susceptibility with respect to response.

The primary outcome is defined as “cure” or “no cure” of a lesion at 3 years, i.e. a binary variable. From previous experience it is expected that the reference treatment leads to a probability of cure of 80 %.

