## **8.3 Justification of Sample Size**

The cure rate at 3 years with conventional treatment (5, 6) is expected to be 85 %. The study aims to detect an experimental success rate that is less than 75 % (i.e. a non-inferiority margin of 10 %). With a significance level of 5% and a power of 80% a sample size of 170 lesions per group is required (ref StatExact 8, Cytel Corp. USA). To accommodate some loss to follow-up, we aim to recruit a total of 187 lesions in each group.

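### The reference cure rate is 80% in the synopsis and 8.2.1 but 85% in 8.3, and the 170 lesions per group that the synopsis and 8.3 share gives about 74–75% power at 80%, not the stated 80%

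*Protocol*

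**What the plan says.** Three places in the protocol give the planning rate for the reference regime.

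- Synopsis, Statistics: "The expected cure rate at 3 years (reference) is set to 80" per cent. The lowest acceptable result is given as "an experimental success rate of no less than 70 % (the non-inferiority margin 10" per cent).
- Section 8.2.1, which defines the binary primary outcome: "From previous experience it is expected that the reference treatment leads to a probability of cure of 80" per cent. This section gives no floor, sample size or power.
- Section 8.3: "The cure rate at 3 years with conventional treatment (5, 6) is expected to be 85" per cent, with the aim put as "an experimental success rate that is less than 75 % (i.e. a non-inferiority margin of 10" per cent).

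The synopsis and 8.3 both state 170 lesions per group, 5% significance and 80% power. Neither says whether the 5% is one-sided or two-sided. Section 8.3 raises recruitment to 187 per group for loss to follow-up.

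Section 8.2.2 fixes a non-inferiority hypothesis with a margin of 0.1 (null: regime 1 is worse than regime 2 by at least the margin) and plans a two-sided 95% confidence interval for the difference. The synopsis describes the capability of the design differently: "a difference between the two treatment regime groups of at least 10% can be found".

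**The concern.** With a fixed absolute margin, the required sample size is proportional to p(1−p). That is 0.85 × 0.15 = 0.1275 at 85% and 0.80 × 0.20 = 0.16 at 80%. The ratio is 0.16/0.1275 = 1.25, so a design at 80% needs about a quarter more lesions for the same power. One figure of 170 cannot give 80% power at both rates, so at least one of the two justifications must be wrong on its own inputs.

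What is at stake is the chance that the trial ends inconclusive when the two regimes are in truth equally good. A reader of the synopsis would put that chance at 20%. The wording of the aim adds to the difficulty, because neither sentence states what the test in 8.2.2 can show.

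**Working it through.** **Inputs.** Reference rate 80% (synopsis, 8.2.1) or 85% (8.3); margin δ = 0.10 (synopsis, 8.2.2, 8.3); n = 170 per group, 5% level and 80% power (synopsis, 8.3); 1:1 allocation (synopsis, 187 in each group). Two assumptions are not stated in the protocol: equal true rates in the two regimes, and independent lesions.

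**Formulas (normal approximation).**
n per group = (z₁₋α + z₀.₈₀)² × 2p(1−p) / δ²
Power = Φ( δ / √(2p(1−p)/n) − z₁₋α )

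**Step 1: reproduce 170 at 85%, one-sided 5%.**
n = (1.645 + 0.842)² × 0.255 / 0.01 = 158.
Power at 170: √(0.255/170) = 0.0387; 0.10/0.0387 = 2.582; 2.582 − 1.645 = 0.937; Φ = 82.6%.
Section 8.3 cites an exact-methods package. An exact unconditional score test has 79.8% power at n = 165 and 81.0% at n = 168, so it crosses 80% just below 170. The figure in 8.3 is therefore reproduced at 85% with a one-sided 5% test.

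**Step 2: the synopsis inputs, 80%, one-sided 5%.**
Power at 170: √(0.32/170) = 0.0434; 0.10/0.0434 = 2.305; 2.305 − 1.645 = 0.660; Φ = 74.5%.
n for 80% power = (2.487)² × 0.32 / 0.01 = 198. The Farrington–Manning score method gives 201. The exact test gives 79.4% at 202 and 80.7% at 205, so about 205.

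**Step 3: one-sided 2.5%, which is what a decision by the two-sided 95% interval implies.**
Power at 170: 2.582 − 1.960 = 0.622, Φ = 73.3% at 85%; 2.305 − 1.960 = 0.345, Φ = 63.5% at 80%.
n for 80% power by the same formula: 201 at 85% and 252 at 80%.

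**Power with 170 per group, by method:**

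| One-sided level | True rate | Normal approx. | Farrington–Manning | Exact |
|---|---|---|---|---|
| 5% | 85% | 82.6% | 81.5% | 81.3% |
| 5% | 80% | 74.5% | 74.1% | 73.6% |
| 2.5% | 85% | 73.3% | 71.7% | 71.7% |
| 2.5% | 80% | 63.5% | 62.9% | 62.0% |

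**Step 4: all 187 per group evaluable, 80%, one-sided 5%.** 78.0% by normal approximation and 77.2% exact, still under 80%.

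**Step 5: the wording of the aim.** The alternative in 8.2.2 is that regime 1 is less than 10 points worse than regime 2. With a reference of 85%, that means a regime 1 rate above 75%. Section 8.3 says "The study aims to detect an experimental success rate that is less than 75" per cent, which lies in the null region. The synopsis floor runs in the right direction, but its later sentence speaks of finding a difference, whereas the test is meant to exclude one.

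**The case against.** The best defence is that section 8.3 is the formal justification and is sound on its own terms: 85%, one-sided 5% and 170 per group are consistent. That stands. It means the false power figure sits in the synopsis alone. Section 8.2.1 conflicts on the rate but makes no power claim, so it would be wrong to say that all three places rest on 170.

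A reader might infer that 170 belongs to 85% whatever the test. The documents do not support this, because the sidedness is unstated. At one-sided 2.5%, 170 falls short of 80% power at both rates. That further loss comes from the choice of level, not from the 80/85 conflict, and the two effects should be kept apart.

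A reader might also take the synopsis sentence about finding a 10% difference as a superiority claim and judge the trial's power on that basis. The documents do not support this either. The sentence just before it names a non-inferiority margin, 8.3 does the same, and 8.2.2 fixes a non-inferiority hypothesis. No superiority test is planned, so the fault there is one of description.

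It can fairly be added that the allowance to 187 softens the loss. It does so only if no lesion is lost, which is what the allowance is meant to cover.

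**Conclusion.** The contradiction is real and nothing in the protocol resolves it. On the synopsis's own inputs the stated 80% power is not reached under either sidedness. It is about 74–75% at one-sided 5%, some 6 points short, and about 62–63% if the 95% interval decides, some 17 points short. At 85% the claim holds at one-sided 5% (about 81–83%) but not at one-sided 2.5% (about 72–73%). Separately, the aim in 8.3 is reversed, and the synopsis sentence does not describe the hypothesis in 8.2.2.

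The figures assume equal true cure rates and independent lesions. Section 4.1 plans 374 lesions in 277 patients, and 5.2 alternates regimes within a patient, so they are approximate. The documents do not show which of the two rates is the better expectation. The rate conflict concerns planning only: it leaves the test and its type I error as they are.

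**What to change.** 1. State one 3-year reference cure rate, with its basis, in the synopsis, 8.2.1 and 8.3, and derive the floor from it.
2. State whether the 5% is one-sided, and make it consistent with the confidence interval in 8.2.2 that will carry the decision.
3. Keep 170 evaluable (187 recruited) lesions per group, and report the power this gives at both 80% and 85% for the chosen level, with the assumptions of equal true rates and independent lesions written down.
4. Replace the aim sentence in 8.3 and the sentence on finding a difference in the synopsis with: the trial aims to rule out that the regime 1 cure rate is more than 10 percentage points below that of regime 2, assuming equal true rates.

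The cost is editorial, plus a less favourable stated power. Holding 80% power at an 80% rate would instead need about 198–205 evaluable lesions per group at one-sided 5%, which is a change of size and not of wording.

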## LIST OF ABBREVIATIONS

|                     |                                                              |
|---------------------|--------------------------------------------------------------|
| AE                  | adverse event                                                |
| BCC                 | basal cell carcinoma                                         |
| CR                  | complete response                                            |
| EC                  | ethics committee                                             |
| EMA                 | The European Agency for the Evaluation of Medicinal Products |
| GCP                 | Good Clinical Practice                                       |
| ICH                 | International Conference of Harmonisation                    |
| J                   | Joule                                                        |
| non-CR              | non-complete response                                        |
| MedDRA              | Medical Dictionary for Regulatory Activities                 |
| METVIX ® | methyl 5-aminolevulininate hydrochloride                     |
| PDT                 | photodynamic therapy                                         |
| PpIX                | protoporphyrin IX                                            |
| SAE                 | serious adverse event                                        |
| SDV                 | source data verification                                     |
| UV                  | ultraviolet                                                  |
| CRF                 | case report form                                             |
| LED                 | light emitting diode                                         |
| ITT                 | intend to treat                                              |
| PP                  | per protocol                                                 |

All dimensional units are in standard SI units.

# 1. INTRODUCTION

## 1.1 Clinical Experience

Basal cell carcinoma (BCC) is the most common malignant skin lesions in the adult, white population (1). It is a slow-growing tumour, which despite low metastatic potential can cause significant local tissue destruction and patient morbidity(2). Nodular BCCs are typically pearly pink or flesh colored papules or nodules with telangiectasia. The superficial type occurs in varying numbers and size as reddish patches with sharp and irregular borders and showing fine scaling or crusts. Given that BCC has a predilection for sun-exposed skin on head, face and neck, cosmetic outcome is significant for choice of therapy

The most common modalities in the treatment of BCC are surgery, cryotherapy, curettage and electrodesiccation, radiotherapy, local chemotherapy and photodynamic therapy (PDT)(3). Metvix® cream 160 mg/g (Galderma, France) (MAL) was approved for marketing in Norway in 2003 for methyl-aminolevulinat (MAL)-PDT and is today commercial available in more than 30 countries worldwide. Metvix® is a marketed product for treatment of actinic keratosis, BCC and Bowen's disease.

PDT exerts the selective destruction of abnormal cells through light activation of a photosensitizer in the presence of oxygen. The photosensitizer generates reactive oxygen species upon illumination with red light that causes tissue destruction and necrosis(4). As BCC lesions are usually located to cosmetically sensitive skin areas, PDT is an attractive treatment modality, which also allows treatment of large areas, with a high response rate and excellent cosmetic result (5, 6).

Conventional PDT of BCC lesions include 3 hours methyl aminolevulinat (MAL) cream application under occlusion, leading to high and selective accumulation of photoactive porphyrins in the BCC lesions. The porphyrins are then activated by red light illumination, thus starting a photochemical reaction which leads to cell necrosis and apoptosis. MAL-PDT for BCC is currently approved for a procedure using two treatment sessions one week apart, and is therefore considered quite time- and resource-consuming. Introducing a single treatment session, with a new PDT session for treatment failures after 3-month, might represent an attractive simplification.

Treatment with PDT has been shown to be effective for BCC with tumour clearance rates using ALA- and MAL-PDT ranging from 76 % to 100 % in superficial lesions and from 64% to 92% for nodular tumours, which are comparable to results shown with other more established treatment modalities for BCC. The best results for nodular BCCs have been obtained by repeated ALA-PDT treatment sessions, leading to 100% cure rate in 25 tumours (7). Routine double treatment sessions are today an acknowledged practice as considered to contribute to a high treatment response (8).

Results from various PDT studies are difficult to compare because the treatment procedures are not standardized and information on tumours characteristics are often lacking. However, the experience from clinical experience and reports from several studies indicate that a significant number of BCC only require one treatment session (6). In a randomized 5-year follow-up study a high 75% complete response rate after one session of PDT was demonstrated in superficial BCC (9). This is promising and suggests that all tumours are not

in need of a second treatment. Introducing a single treatment session, with a new PDT session only for those tumours showing treatment failures after 3-month, might represent an attractive simplification of the current regime.

One of the challenges with topical PDT is the treatment of thick BCC lesions. The delivery of sufficient photosensitizer and light to the full depth of the lesion is critical. Improved treatment response can be achieved by careful lesion preparation(10).

Recent studies have suggested that the recurrent tumours often appear among lesions located within the central face (H-area), large lesions and among recurrent lesions themselves. Some subtypes of BCC tumour appear to have a reduced response to PDT. Morpheic BCCs, surrounded by abundant collagen fibres, generally do not respond well to topical PDT (11). Furthermore, the diminished treatment results of pigmented BCC are most likely due to inhibition of melanin molecules on the light penetration. Long-term efficacy of PDT among various BCC subtypes and tumour of various thickness is needed. The use of immunohistochemical stains may allow for an enhanced detection of tumours more resistant to therapy (12).

## **1.2 Benefits and Risks**

Metvix® PDT is an approved and marked treatment modality for patients with pre-malignant disease and BCC.

General benefits of topical Metvix® PDT include:

- Non-invasive treatment available on an outpatient basis
- Several separate lesions can be treated simultaneously
- The same lesion(s) can be treated repeatedly with success
- Excellent cosmetic results
- No known toxicity or interaction with other medication
- Lesion selective, leaving the surrounding tissue intact
- No skin photosensitization after 24 hours
- Only minor, manageable local side effects related to treatment site

Study benefits include the following:

If the effect of the new, alternative and simpler treatment regime proves as effective as the standard approved regime MAL-PDT will be an even more attractive therapy alternative for low-risk BCC. The treatment will be easier to manage with improved cost-effectiveness as well as reduced discomfort and fewer side effects for the patients.

The risks attributed to Metvix® PDT are few and related mainly to transient discomfort and pain during and shortly after illumination. Inflammation following tumour destruction may give local, transient erythema and oedema. Treatment of large lesions may cause severe erythema, followed by ulceration. These side effects normally last for a few days, in rare occasions up to a week after treatment.

Standard Metvix® PDT in BCC is today given as two treatment sessions separated by one week. Patients with non-complete response after one PDT session in treatment regime 1 are offered an additional PDT at the 3-month control. The possible delay of the second session of BCC treatment is acceptable, as BCC grows very slowly

Patients with non-complete response after either PDT treatment regimes at the control visit 3 months after the latest treatment session are withdrawn from the study. They are then offered standard BCC treatment at the discretion of the dermatologist. Patients will receive detailed oral and written information about the risks of side effects. If the patients find the side effects unacceptable, they are free to withdraw from the study at any time and without any further explanation.

### **1.3 Clinical Trial Regulations**

The clinical trial will be conducted in compliance with the protocol, according to ICH E6: Good Clinical Practice: Consolidated guideline, CPMP/ICH/135/95, and national guidelines including Clinical Trials Directive 2001/20/EC.

## **2. OBJECTIVES OF THE TRIAL**

### **2.1 Primary Objectives**

The primary objective of this study is to investigate if a more simple and flexible PDT treatment schedule (one single treatment session with re-treatment of non-complete responders-regime 1) for low-risk primary superficial or nodular BCC will be as effective as the standard and approved two-treatments one week apart (regime 2).

### **2.2 Secondary Objectives**

To investigate relationship between clinical and pathological tumour characteristics and the relationship between tumour recurrence rates with tumour thickness and histopathological subtypes and various immunohistochemical markers.

